### Randomization and sampling procedure

Among the 15 districts in Eastern Hararghe Zone, Haramaya and Kombolcha are selected purposefully because they have better access to electric power and network, which are mandatory for mobile-phone charging and communication during the study period. In addition, the community in these districts has similar socioeconomic and demographic characteristics and maternal health care service coverage [19, 20]. Then, by a lottery method, the two districts are determined as an intervention (m-health + SOC) or a control group (SOC only). Accordingly, Haramaya district is an intervention group (m-health + SOC) whereas Kombolcha is a control (SOC).

Based on the EHSTP of 2016–2020, one HC, which encompasses five HPs in five Kebeles which consisting of 3000–5000 people each, can provide service for 15,000–25,000 people [21]**.** In Ethiopia, the estimated number of pregnancies in a given population is about 4.6% [22]. Hence, the total number of estimated pregnant mothers in five kebeles surrounding one HC is about 690–1150.

Among the seven HCs in Haramaya district, Addelle HC is selected by the purposive method as secondary study unit. The main reason for the purposive selection is accessibility of electric power and network, which will be mandatory for mobile-phone charging and communication during the study period. Finally, all pregnant mothers who fulfill the enrollment criteria in the selected Kebele will be registered and 320 pregnant mothers will be selected for the intervention group by a simple random-sampling method. Likewise, of the five HCs in Kombolcha district, Kombolcha HC is selected purposefully for the same reason, and from the surrounding kebeles, 320 mothers will be selected for the control group by simple random sampling (SRS) method.

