**Methods/design:**

Through, a cluster-randomized controlled trial, 640 participants will be selected based on their districts and respective health centers as the unit of randomization. All pregnant mothers who fulfill the inclusion criteria will be allocated to a mobile-phone-based intervention and existing standard of care or control with a 1:1 allocation ratio. The intervention consists of a series of 24 voice messages which will be sent every 2 weeks from the date of enrollment until the close-out time. The control group will receive existing standard of care without voice messages. Data related to outcome variables will be assessed at three phases of the data collection periods. The primary outcome measures will be the proportion of antenatal care visits and institutional delivery, whereas the secondary outcome measures will consist of the proportion of postnatal care visits and pregnancy outcomes. Risk ratios will be used to a measure the effect of intervention on the outcomes which will be estimated with 95% confidence interval and all the analyses will be done with consideration of clustering effect.

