## Methods/design

### Study design

A single-blind, cluster-RCT study design will be employed on districts and their respective health centers (HCs). Study participants will be randomized to a mobile-phone-based intervention (voice message for reminding and informing about the advantages of maternal health care service use) or existing standard of care (SOC)/control (without voice message) under their respective districts and HCs with a 1:1 allocation ratio (Fig. 1).

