### Statistical method

For primary and secondary outcomes, Relative Risk with 95% confidence interval will be estimated. The association of dependent and independent variables will be checked by using the chi-square test. For count data, further analysis will be done by using multivariate count data logistic regressions or the Poisson Regression Model will be used to examine the effect of treatment on trial arms and Kaplan-Meier survival analysis will be used to compare maternal health care service use over time among treatment and control groups. Moreover, to adjust for both the clustering effect of the districts with their respective HCs and the participant-level intracluster correction, Generalized Estimating Equation (GEE) models will be used. All the analysis will be done by using STATA software.

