Randomized controlled trial studies, which were conducted in Zanzibar, Kenya and Nigeria at different times to evaluate the effect of m-health on maternal health care service utilization, have shown a promising outcome on maternal health care service utilization [16, 28, 32, 33]. However, in all aforementioned investigations the study participants were recruited from health facilities which may not show the effect of m-health on early initiation of maternal health care service use. Thus, for the current study, recruitment and enrollment of the study participants will be conducted at the community level. In addition, this investigation will enroll only those mothers at less than 16 weeks of GA to test the effectiveness of m-health on early initiation of maternal health care service use and its uptake. It is also recognized that m-health is a dynamic issue with the fast transfer in both technology and information literacy for developing countries. Hence, there is a need to examine what works or does not work yet and to establish a standard in this area. Therefore, this mobile-phone-based voice message trial study should generate strong evidence on maternal health care service utilization in resource-limited settings with poor literacy, which can be generalizable to similar populations in various settings.

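### One district and one health centre per arm: treatment is aliased with district, the planned GEE cannot adjust for that, and the power and generalisability claims do not hold as written

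*Protocol article*

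**What the plan says.** The abstract says that "640 participants will be selected based on their districts and respective health centers as the unit of randomization". Study design describes a cluster-randomised trial on districts and their HCs, and continues: "Study participants will be randomized to a mobile-phone-based intervention" or standard of care, under their respective districts and HCs, 1:1.

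Randomization and sampling procedure gives the actual steps. Two districts are chosen purposively, for power supply and network. "Then, by a lottery method, the two districts are determined as an intervention (m-health + SOC) or a control group (SOC only"), with the result that "Haramaya district is an intervention group (m-health + SOC) whereas Kombolcha is a control (SOC"). Next, "Among the seven HCs in Haramaya district, Addelle HC is selected by the purposive method as secondary study unit"; in Kombolcha, one of five HCs is likewise chosen purposively. In each arm 320 eligible women are then drawn by simple random sampling.

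For analysis, Statistical method plans relative risks, chi-square tests for associations, and, "to adjust for both the clustering effect of the districts with their respective HCs and the participant-level intracluster correction, Generalized Estimating Equation (GEE) models". The sample size sections inflate by a design effect of 1.3 to reach 320 per arm for 80% power, without giving an ICC or a cluster size. The Background explains the choice of two districts 34 km apart as a guard against contamination. The Discussion expects that the trial "should generate strong evidence on maternal health care service utilization in resource-limited settings with poor literacy, which can be generalizable to similar populations".

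**The concern.** A cluster trial separates treatment from cluster differences by having several clusters per arm. The spread between clusters within an arm tells the analyst how much two arms would differ with no treatment effect. Here each arm has one district and one HC, so that spread is never observed. Any existing difference in service use between the two areas enters the relative risk as if it were an effect of the messages, and enrolling more women per district does not shrink it.

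The protocol treats the problem as solved twice, by the design effect and by GEE. If neither does the job, a reader will take a two-site contrast for a cluster-adjusted randomised result. The stated similarity of the districts does not settle this. Study setting itself reports 18.46% urban residents in the intervention district against 9.01% in the control district, and lists a hospital only in the intervention district. Both could bear on institutional delivery, a primary outcome.

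**Working it through.** **Inputs from the protocol.** Control 47%, intervention 60%, two-sided 5%, 80% power, design effect (DE) 1.3, 320 per arm; two districts, one per arm; one HC per district. **Assumed:** district ICC of 0.005, 0.01 or 0.02, because none is given.

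**1. The stated sample size.** The two-proportion formula with continuity correction gives 246 per arm; 246 × 1.3 = 319.8, rounded up to 320. Without the correction, 230 × 1.3 = 299, which does not match. So the stated figure reproduces, and the arithmetic is not at fault.

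**2. What DE 1.3 covers.** DE = 1 + (m − 1) × ICC. With one cluster of m = 320 per arm, 1.3 implies ICC = 0.3/319 = 0.0009.

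**3. Information at the level of randomisation.**
- Cluster-level df = 2 clusters − 2 arms = 0.
- A design matrix of intercept, treatment and district has rank 2, not 3, so the two effects cannot be separated.
- Only two allocations are possible. The smallest randomisation p-value is 0.5 one-sided and 1.0 two-sided, at any sample size.

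**4. GEE clustered on district.** The sandwich variance is A⁻¹BA⁻¹, where B sums the squared cluster scores. With treatment as the only regressor, each arm's fitted mean equals its district's mean, so each cluster score Σ(y − μ̂) is zero and B = 0. A Poisson GEE on simulated data (60% v 47%, 320 per arm) gave a log relative risk of 0.312 with a robust SE of about 2 × 10⁻¹⁶ under independence and 3 × 10⁻¹⁶ under an exchangeable structure. With one participant-level covariate the SE was no longer zero, but it varied over orders of magnitude between fits, from about 0.00001 to around 0.01. Taking participants as the clusters gave about 0.08.

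**5. Chance difference between two districts, no treatment effect.** SD = √(2 × ICC × 0.47 × 0.53). False-positive rate of an unclustered test ≈ 2[1 − Φ(1.96/√DE)]; of a test that allows for DE 1.3 ≈ 2[1 − Φ(1.96 × √(1.3/DE))].

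| District ICC | DE at m = 320 | SD of difference | False positives, unclustered | False positives, allowing DE 1.3 |
|---|---|---|---|---|
| 0.005 | 2.6 | 5.0 points | 22.4% (simulated 22.6%) | 16.5% |
| 0.01 | 4.2 | 7.1 points | 33.8% (simulated 34.1%) | 27.5% |
| 0.02 | 7.4 | 10.0 points | 47.1% (simulated 47.7%) | 41.1% |

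**6. Using kebeles as clusters under the present lottery.** This does not rescue the test. Assuming 5 kebeles per arm, 64 women each and kebele ICC 0.005, a kebele-level t-test rejects falsely 5% of the time if district variance is zero, but about 16%, 25% and 37% at district ICC 0.005, 0.01 and 0.02.

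**7. Randomising kebeles instead.** Assume 10 kebeles of 64 women, 5 v 5. SE = √[(0.47 × 0.53 + 0.60 × 0.40)/320 × (1 + 63 × ICC)], referred to t with 8 df.

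| Kebele ICC | SE | 0.13/SE | Power |
|---|---|---|---|
| 0.005 | 0.0448 | 2.90 | 72% |
| 0.01 | 0.0499 | 2.60 | 63% |
| 0.02 | 0.0588 | 2.21 | 49% |

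In this layout DE 1.3 covers an ICC of 0.3/63 = 0.0048.

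**The case against.** The Background gives a reason for the design: two districts 34 km apart limit contamination. Randomising neighbouring kebeles around one HC would undo that, since women in both arms would use the same HC, whose staff also track deliveries. Nothing in the protocol shows that message sharing would be slight. This stands, and it makes kebele randomisation a trade-off. So does its power: a reader might infer that the same 640 women would suffice, but step 7 shows that they would not give 80% at these ICCs. Five kebeles per HC is also a national planning norm in the protocol, not a count for these sites.

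Several stronger readings of the defect are tempting and are not supported:
- That the planned GEE always returns a zero SE. This holds for the unadjusted model clustered on district; the protocol lists covariates, and with them the SE is small but not zero.
- That 23% to 48% is the error rate of the planned primary analysis. Those rates belong to an unclustered test under assumed ICCs. The protocol uses chi-square for associations and says that all analyses will consider clustering.
- That Study design claims individual randomisation outright. Its sentence continues with the districts and HCs and follows a description of a cluster trial. It is loose wording that needs correcting.
- That the districts are known to differ in staffing or distance to care. Only urban share and the hospital are documented, and the protocol otherwise asserts similarity from sources not shown.

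None of this touches the aliasing itself.

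**Conclusion.** The design and the stated adjustment do not fit together. Treatment is fully aliased with district and HC, GEE cannot adjust for that, and DE 1.3 allows for almost no between-district variation. The 80% power and the claim of strong, generalisable evidence are wrong as written.

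A reader might go further and infer that no valid test of any kind exists. The documents support a narrower conclusion. No valid test exists at the level of randomisation. A participant-level test is valid if between-district variance is zero, an assumption that the trial's data cannot check and that the protocol's own district figures make doubtful.

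The aliasing, the zero degrees of freedom and the failure of GEE need no assumption beyond the stated procedure. The SDs of 5 to 10 points and the false-positive rates rest on the assumed ICCs. The direction of any bias is unknown.

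**What to change.** **If the district lottery is kept:**
1. Delete the statement that GEE adjusts for district and HC, and do not cluster GEE on district.
2. State that the 80% power and all intervals are conditional on no between-district variance.
3. Describe the study as a comparison of two districts.
4. Correct Study design to say that districts are allocated and women are sampled within them.
5. Remove the claims of strong and generalisable evidence from the Discussion.
6. Adjust the primary model for previous service use collected at Phase I, noting that this reduces measured imbalance and does not break the aliasing.

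The cost is wording and one model term; no extra women or data.

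**Option for the sponsor to weigh,** since Trial status says that participant selection has not started: randomise kebeles, or several HCs, within both districts. Kebeles would be analysed as the clusters, with a small-sample correction. This breaks the aliasing, and its costs must be stated: possible contamination, which the protocol set out to avoid; a kebele count to be confirmed locally, with five per HC splitting 3:2 and 2:3; and power of about 72%, 63% or 49% for 10 kebeles of 64 women at kebele ICC 0.005, 0.01 or 0.02. The stated 80% would have to be restated, or more clusters added.

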### Participants: inclusion and exclusion criteria

The participants will be recruited from two districts (Haramaya and Kombolcha districts) based on pre-set eligibility criteria (pregnancy, gestational age (GA), ownership of a mobile phone and willingness to participate). The participant will be included in the trial if her GA is less than 16 weeks, she owns a mobile phone and has willingness to participate. The potential trial participants will be identified by the field worker-based enrollment criteria. For all eligible participants, the field workers will explain about study by reading the participant information sheets; if the study subjects are willing to participate, written informed voluntary consent will be obtained and baseline data collection will be made.

In this trial, study women who fulfill the enrollment criteria for the study but are critically ill at time of enrollment will be excluded from the study. Critically ill women are those pregnant mothers who unable to respond to interview questions because of illness. In addition, women with any systemic illness during this time will be excluded from the study. Any pregnant women with systemic illness need an special ANC follow- up, which is different from the recommended routine ANC follow -up and this set precondition without effect of treament for good adherence to maternal health care service use. Hence, any pregnant mother with known systemic illnesswill be excluded from this study.

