### Data quality control

In this investigation, mobile-phone-based voice message will be used for reminders of ANC and PNC follow-up appointments and EDD with information about their advantages. This message will be sent in the local language (Oromiffa) and integrated into regular automatic mobile voice messaging at every 2-week interval. The content of the voice messages will be recorded on m-health mobile phones for all who are conducting the study for pregnant mothers under the interventions. Moreover, all enrolled mothers will be oriented as they will receive voice messages regularly from the date of enrollment for appointment reminders.

Data collectors will be given a 5-day intensive training on the contents of data collection tools and data collection procedures. The questionnaire will be prepared in English and translated into the local language for interview purposes and back into the English language for data analysis and to maintain consistency of information. The data will be checked for completeness at all stages of the data collection and possible errors will be returned to the data collectors for correction. Furthermore, a focal person will be assigned to study sites throughout the study period as supervisors and, every 2 weeks, the activities will be audited by the investigators and recorded. Network and electricity challenges will be settled with a systematic way of shifting time of communication without deleting the number of communications. The pre-test will be done on 5% of the total sample size away from the actual study site. Moreover, an independent quality control team will monitor the quality of the treatment or intervention. This team will visit the study process three times (at the start of the intervention, midterm of the intervention and at the end line) until the investigation is completed.

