### Trial status

Implementation of the study will be started in August 2017. At this time participant selection has not started.

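### The district allocation is known before any woman is screened or consented, and nothing described conceals the arm, so consent may differ between arms

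*Protocol article*

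**What the plan says.** Under Randomization and sampling procedure, the protocol allocates whole districts: "Then, by a lottery method, the two districts are determined as an intervention (m-health + SOC) or a control group (SOC only". It then gives the outcome of the draw: "Accordingly, Haramaya district is an intervention group (m-health + SOC) whereas Kombolcha is a control (SOC". Under Trial status it adds: "At this time participant selection has not started".

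Entry of individual women comes later. Under Participants: inclusion and exclusion criteria, a woman qualifies if her gestational age is below 16 weeks and "she owns a mobile phone and has willingness to participate". Field workers identify candidates, and "the field workers will explain about study by reading the participant information sheets"; then, "if the study subjects are willing to participate, written informed voluntary consent will be obtained and baseline data collection will be made".

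Under Screening and enrollment procedure, women in the selected kebeles who own a phone, have amenorrhea and use no family planning are all to be tested for pregnancy. Those found eligible are registered, and 320 per arm are drawn from a computer-generated random table.

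Study design calls the trial single-blind without saying who is blinded. Under Data quality control, "all enrolled mothers will be oriented as they will receive voice messages regularly from the date of enrollment".

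**The concern.** In a cluster trial that recruits after allocation, randomization does not protect the step at which individuals enter. If the offer of messages appeals more to women already inclined to use facility care, or if field workers present the study differently in the two districts, the enrolled groups can differ in their underlying tendency to attend antenatal care and deliver in a facility. That difference would look like an intervention effect.

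Both primary outcomes are exposed, because both measure care-seeking, which is the trait most likely to drive willingness. Intention-to-treat analysis preserves the groups as enrolled. GEE deals with correlation within clusters. Neither acts on who was enrolled.

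The problem is separate from having one district per arm. More districts would average out district differences, but not a consent difference that follows the arm.

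**Working it through.** **Order of events.** (1) The lottery is drawn and its result printed (Randomization and sampling procedure). (2) No participant has yet been selected (Trial status). (3) Pregnancy testing, gestational-age assessment and registration follow (Screening and enrollment procedure). (4) Information, consent and baseline are carried out by field workers, with willingness as a criterion (Participants). No section between (1) and (4) describes concealing the arm from field workers or from women.

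**What the safeguards reach.** Testing every phone owner with amenorrhea who uses no family planning, then sampling at random, leaves recruiters little room to choose individuals. Refusal is a different matter. The text does not settle whether consent comes before or after the draw. If before, the draw is from women already filtered by willingness. If after, refusals filter the women drawn. Either way consent is sought in a district whose arm is fixed.

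**The plan's own sample size.** Inputs from Sample size determination and the assumptions that follow it: 47% against 60%, two-sided 5%, 80% power, design effect 1.3. The two-proportion formula with continuity correction gives 246 per arm, and 246 × 1.3 = 319.8, rounded up to 320. The stated figure reproduces and is not in question. Effective size per arm is 320 / 1.3 = 246.

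**Illustration of size.** The documents give no consent rates, so these are assumptions: no true effect; 47% facility delivery in control with no selection there; in the message district, consent c_u = 95% among women who would deliver in a facility, and c_n = 80% or 70% among the others.

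Rate among enrolled women = p·c_u / [p·c_u + (1 − p)·c_n], with p = 0.47:

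- c_n = 80%: 0.4465 / (0.4465 + 0.4240) = 51.3%; risk ratio 51.3 / 47 = 1.09.
- c_n = 70%: 0.4465 / (0.4465 + 0.3710) = 54.6%; risk ratio 54.6 / 47 = 1.16.

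Rejection probability of the two-sided 5% z-test, with d the gap, SE0 the pooled and SE1 the unpooled standard error: Φ[(d − 1.96·SE0)/SE1] + Φ[(−d − 1.96·SE0)/SE1].

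| Consent among others | Enrolled rate | Gap d | Effective n 246 | n 320 |
|---|---|---|---|---|
| 95% (no selection) | 47.0% | 0 | 5% | 5% |
| 80% | 51.3% | 4.3 points | 16% | 19% |
| 70% | 54.6% | 7.6 points | 39% | 49% |

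Against the 13-point difference the trial is sized to detect, the assumed gaps are 4.3 / 13 = 33% and 7.6 / 13 = 58%. The design effect widens the variance but leaves the bias where it is.

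**The case against.** A reader might infer that women know their arm when they decide whether to join. The documents do not show this. The information sheet is not reproduced and may be neutral as to arm, and the single-blind label could mean that women are kept unaware. Knowledge on the part of field workers is a fair inference from a printed allocation; knowledge on the part of women before consent is not established. The sentence on orientation about messages does not settle it, because it concerns women already enrolled and follows a sentence about mothers under the intervention.

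A reader might also infer that the sampling register consists only of willing women. Screening and enrollment procedure names pregnancy, gestational age and phone ownership as the main criteria; willingness appears under Participants, and its place relative to the draw is unclear. The universal screening and the random draw are real safeguards against hand-picking.

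The consent rates in the illustration have no source in the documents, and the result depends heavily on them: the milder case gives 16% to 19% rejection, not 39% to 49%. The illustration covers institutional delivery only. Previous maternal care use is collected at baseline (Outcome measures), so imbalance could be examined and partly adjusted for. Finally, with one district and one health center per arm, this bias cannot be separated from a district difference, so removing it would not by itself make the comparison interpretable.

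All of this stands as a limit on how strongly the point can be put. It does not remove the point: the order of steps is as printed, no concealment is described, and neither safeguard prevents refusals from differing by arm. Adjustment would reach only what is measured.

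**Conclusion.** The point holds as a risk of differential consent by arm, not as a demonstrated bias. It rests on three things in the text: the allocation is fixed and printed before any woman is selected, willingness is required for entry, and no step conceals the arm. Under the assumed consent rates, with no true effect, the spurious risk ratio would be 1.09 or 1.16, and the chance of a significant result 16% or 39% at effective n 246 per arm (19% or 49% at n 320), instead of 5%. These figures show what modest selection could do; they do not estimate what will happen. An analysis plan cannot undo the order of recruitment, so the correction belongs in the protocol, before enrolment starts.

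**What to change.** - In Participants and in Screening and enrollment procedure, state that one identical, arm-neutral information sheet and script is used in both districts, and that for each woman eligibility, consent and the Phase I baseline are completed before she is told her arm. Say whether consent precedes or follows the random draw.
- In Data quality control, limit the orientation about messages to arm A women, after baseline.
- Keep the arm from field workers as far as is practicable, given that the allocation is published.
- Record the numbers screened, eligible, sampled and refusing by district.
- Compare baseline characteristics between arms; Outcome measures at present states only a comparison with the general population. Adjust the primary analysis for previous maternal care use, which is already collected.

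The cost is separate handling of the disclosure step and a short log. Redrawing the lottery is not proposed: the result is published, and a second draw would raise its own question of integrity. Nor is withholding the arm until both districts finish enrolment, because messages run from each woman's enrolment, before 16 weeks, and would be delayed. Some bias remains if the arm is known locally, and the separate problem of one district per arm is untouched.
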